## Methods

### Study setting

The study is conducted in Siaya County, Kenya, located on the shores of Lake Victoria, in the West of the country. Siaya County has a population of 984,069 people and is made up of six sub-counties, which are mostly rural and perform poorly on several development and health indicators [21]. As a whole, the County has a human development index (HDI) score of 0.46, significantly below the national average of 0.56 [22]. It has the highest national rates of HIV infection, TB and malaria in Kenya, and among the worst indicators of child and overall health status [23]. Infant mortality stands at 111 per 1000 live births against 49/1000 for the country, and maternal mortality at 695 per 100,000 live births against 488/100,000 in Kenya. On a few indicators, the County performs better than the national average. For instance, 38% of the population in Siaya live below the poverty line, while the country’s average is 45% [24]. The rate of immunization in children under 1 year is 72.5% against 67.5% for the country, and the rate of delivery by a skilled attendant is 69.6% against a 61.2% national average [23].

In 2015, Siaya County had 174 health facilities with 123 categorized as public, 7 as non-governmental, 16 as faith-based and 28 as private [25]. Health facilities in Kenya are graded into 6 levels. Level 1 facilities are found at the community level, facilitate community diagnosis, management and referral to upper facility levels and encourage appropriate healthy behaviours. Level 2 facilities, known as Dispensaries, are the interface between the community and the health system, and offer basic curative, case management, prevention and promotion services and basic ANC. Level 3 Health Centres offer curative and case management services for infectious and chronic illnesses and inpatient care, and may cover a catchment of 10,000 people or more. Level 4 facilities are sub-County Hospitals that serve as secondary care facilities but also offer primary healthcare services such as ANC. Level 5 facilities are County Referral Hospitals and offer a broader spectrum of specialized services. Finally, the level 6 facility is a National Referral Hospital, Kenyatta Hospital in Nairobi [26]. The health facilities in Siaya County include one level 5 hospital and one level 4 facility in each sub-County [27]. The rest are mainly level 3 Health Centres and level 2 Dispensaries staffed by nurses or clinical officers, and level 1 community facilities staffed by community health volunteers (CHVs). Overall, there is low coverage of healthcare in the County, with a physician-to-population ratio of 1: 62,000, and nurse-to-population ratio of 1: 2500 [25].

The implementing project partner, Safe Water and AIDS Project (SWAP- http://www.swapkenya.org/), has been working in the region since 2005 to improve maternal and child health. Their work has focused on level 1 services, which are aimed at empowering Kenyan households and communities to take charge of improving their own health, and fall within the Kenya Essential Package for Health (KEPH) Community Strategy. They work in close collaboration with the Ministry of Health and Siaya County Government. Despite these and several other governmental, non-governmental organization (NGO) and donor funded efforts at community level, there still remains a wide gap in reaching pregnant women with the essential package of services that formal healthcare facilities would routinely deliver to those retained in the continuum of care.

### Trial design

The study is a cluster randomized controlled trial (cRCT) in which 24 clusters are randomized to receive the intervention and 24 clusters are randomized to the control.

#### Cluster size and selection

Level 2 or 3 health facilities are the units of randomization. Level 2 or 3 facilities are comparable and comprise Dispensaries and Health Centres, respectively. While there may be some difference in the services provided at these facilities, only those offering the full profile of antenatal services were considered for inclusion in the study. All eligible clients attending participating facilities during the enrolment period were recruited into the trial, subject to consent. Based on the background data on ANC attendance in the study region, it is expected that each of the 48 clusters will recruit 150 participants into the trial, giving a total sample of 7200 eligible women.

#### Randomization

A master list of 84 eligible level 2 and 3 health facilities in Siaya County was generated in December 2016. The master list was stratified by sub-County, so that selection onto the master list was proportional to the number of facilities in each sub-County. From the stratified master list, a short-list of 60 facilities was randomly selected for potential inclusion in the study. The random selection of the 60 short-listed facilities was thus also stratified by sub-County, with the shortlist in each sub-County proportional to the number of eligible health facilities on the master list for that sub-County. Facilities were selected so that catchment areas did not overlap.

In January 2017, the 60 shortlisted facilities were reduced to a final sample of 48 facilities for inclusion in the trial, 24 in the intervention and 24 in the control arm. The selection of the 48 final facilities included in the trial, and their allocation to intervention or control, took place in a public forum to ensure that the selection and allocation processes were transparent and acceptable to senior management in the County Government. To achieve this level of transparency in the selection process, a public meeting was organized. The County Director and the Medical officer of health (MoH) in charge of each of the six sub-counties in Siaya were invited to attend the meeting and participate in the health facility selection and mapping. Each MoH was asked to bring along the County Records Officer (CRO) and another member of their sub-County Health Management Team (CHMT).

During this meeting, the names of all 60 short-listed facilities were written on individual pieces of paper, folded and placed into six transparent plastic boxes - one for each sub-County. The total target sample of 48 facilities was divided between sub-Counties broadly in proportion to the number of facilities in the master list, but with rounding so that each sub-County had an even number of facilities in the trial. The Health Management Teams from each sub-County were invited in turn to select a piece of paper from their respective box, beginning with the Northernmost sub-County. The first facility selected was allocated to the intervention arm and the second to the control arm, the third to intervention and so on in succession. The name of each selected facility was written on a board, together with the allocation. For each selected facility, the records officer for the sub-county was asked to map the location and catchment area on a large map of the county. If a subsequently selected facility was found to have an overlapping catchment area with a facility previously selected, then the newly selected facility was rejected and another drawn from the box to take its place. This process continued until 48 facilities had been selected and allocated for the trial. This meeting generated a list of 24 intervention and 24 control facilities, with their location and catchment areas mapped to ensure that they do not overlap. In summary, the randomization is stratified by sub-County and ensures equal allocation to study arms within each stratum.

#### Trial participants

Eligible participants are women attending their first ANC visit in public primary healthcare facilities in the study area. The ANC attendance rate for at least one visit is very high in Kenya, and more than 80% in Siaya County [10]. The majority of visits take place at level 2 Public Dispensaries and level 3 Health Centers, where the government has abolished user fees for maternal care since June 2014 [28]. Participant recruitment will not be conducted in private clinics, which levy user fees and are more likely to be visited by a small number of women of higher socio-economic status. Participants will also not be recruited from level 4 or 5 facilities, as this would bias the sample towards more complicated pregnancies or serious health conditions.

Trained and incentivized health staff determine if a pregnant woman meets the study eligibility criteria by administering screening questions at the end of her ANC visit. Criteria for enrolment are:i.Women attending their first ANC visit;ii.Long-term resident of the catchment area served by the health facility, with long-term residence defined as living in the area for at least 6 months; andiii.Women with access to a mobile phone that belongs either to themselves or to a member of their household or person whom they trust. Access to a mobile phone is a project requirement for the cash transfer payments and participant follow up. This requirement was easily met by all women (*n* = 200) during the pilot phase of this project.

If a woman is eligible, the recruiting staff explain the objectives of the study and seek her consent to participate.

Enrolment into the study commenced in June 2017 (Fig. 1) and is ongoing. Initially, the enrolment duration was estimated to be 9 months, with an estimated 816 pregnant women recruited into the study each month, leading to a total sample of 7200 women. However, a nationwide health workers’ strike began in June 2017 shortly after initiation of the study and continued until November 2017. During this period, 18 health facilities continued to provide health services with the support of NGOs, and were able to enrol participants. The remaining 30 health facilities were not operational and only started to enrol participants in November 2017 after the strike had been resolved. As of February 2018, the project has enrolled 2841 pregnant women. At the time of writing, enrolment is expected to proceed until July 2018 or until the sample size of 7200 is reached.

**Fig. 1 Fig1:**
[figure not shown]
Schedule of enrolment, interventions and assessments. *MNCH appointments/visits – Standard maternal and child health visits described in Additional file 1. **Covariates - see Table 1. ***Health outcomes - see Additional file 2. MNCH, maternal, newborn and child health; ANC, antenatal care; PNC, postnatal care

Once enrolled into the study, the participant is followed 341 up until the expected baby is 1 year of age (Additional file 1). Participants who move out of the study location are considered lost to follow up.

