#### Telephone surveys

Data are collected on secondary outcomes, socio-economic characteristics, care seeking and decision-making regarding the cash transfer, using the four follow-up telephone surveys described subsequently. Some data on the primary outcomes are also collected (see Table 1). The surveys are administered to all participants in both the intervention and control groups.

Telephone survey one: after enrolment

The first telephone interview is conducted with all participants as soon as possible after enrolment. This structured questionnaire collects data on socio-economic status, self-rated health and decision-making. Information on the recent health visit is also collected, including cost and time taken to travel to the facility, waiting time, cost of all care received and satisfaction with the care received. The same questionnaire is administered to the intervention and control groups, and the interviewer is blinded to the allocation of the participant.

Telephone survey two: 2 weeks after the EDD, if no facility delivery

A phone survey is conducted with all mothers who delivered babies at home, 2 weeks after their EDD. This survey collects information on delivery date, delivery outcome, who conducted the delivery, self-rated wellness for mother and child and breastfeeding initiation. The interviewer is blind to participant allocation.

Telephone survey three: 6 months after the EDD/child birth

A telephone survey is administered to 50% of participants 6 months after the EDD, to collect data on secondary outcomes such as maternal and child deaths, self-rated health of mothers and infants, exclusive breastfeeding and utilization of family planning methods. This survey also collects information on the last health care visit including the cost of seeking care, purpose of visit, waiting time and visit experience.

A second part of the survey is used to elicit information on the receipt of any conditional or unconditional cash transfer, receipt of *Afya* transfers (in the intervention arm only), how any money received was spent and who decided how the money was spent. The interviewer is not blind to participant allocation, as some questions are related to receipt and utilization of the cash transfers.

Telephone survey four: 12 months after the actual delivery date

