#### Collecting data on visits to facilities outside the study area

The strategies used to collect these data vary according to whether or not the participant is considered high risk. High-risk groups in this study comprise mothers whose ANC records show HIV-positive status, positive malaria smear test and/or other diagnoses of sexually transmitted infection (STI). These diagnoses are likely to require referrals and additional health visits not captured in routine ANC or PNC records. Furthermore, participants with these complications are more likely to be lost to the routine monitoring systems as they might completely shift their ANC, delivery and PNC visits to the referral centers that handle these infections.

We will track all health visits made by high-risk participants only, including those taking place in neighbouring counties outside the evaluation zone. This would be done through extra phone calls to the participants to elicit information on health facilities visited. The study team will then visit those facilities and manually extract health records as described previously. The exception to this case would be if care is sought outside the Western Kenya region, in which case the data will be considered missing in the case of a single instance of care seeking, or the participant will be classed as lost to follow up if they have permanently transferred.

For lower risk participants, we shall incorporate questions relating to the primary outcomes (facility visits, child vaccinations etc.) into the telephone surveys (see Telephone surveys) administered to 50% of participants. This gives participants the opportunity to report visits both outside the study area and within, and we shall also ask whether the participant moved temporarily or permanently outside the study area. By comparing these self-reports with the data on visits within the study area (collected by other means) we will be able to approximately deduce the number of visits made outside the study area. These additional visits will not be verified by the study team as will be done for high-risk participants.

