#### Final analysis

Final analyses will be by intention-to-treat, based on all enrolled mothers who were pregnant during the recruitment period (July 2017 to July 2018) and their children, regardless of whether they received the intervention or not. We will test for differences in the primary outcomes between the intervention and control arms using logistic regression for binary outcomes, and ordinal logistic regression for ordinal outcomes, adjusting for clustering using random effect models.

Provided there is no qualitative difference between the odds ratios for the effect of the intervention across the primary outcomes, then only the summary odds ratio will also be presented. This will be the primary effect measure for the trial. It will be estimated using independence estimating equations because not all participants will be eligible for all outcomes (e.g. vaccination of infants who died) and this approach avoids any implicit imputation of outcomes for ineligible participants.

Besides the issue of ineligible outcomes described previously, there should be no completely missing data on the primary outcomes. If a record of attendance cannot be found in the patient records in the study area, this will be interpreted as failure to attend. However, participants may make visits to facilities outside the study area, often in relation to temporarily or permanently moving to reside outside the study area. As described in Section Collecting data on visits to facilities outside the study area, data on visits outside the study area will be available for all higher-risk participants, and dependent on telephone interviews also available (though approximate) for up to half the lower-risk participants.

We plan to conduct our primary analysis based only on data on lower-risk participants from visits within the study area if it seems this will not lead to bias, but to use the approximate number of visits outside the study area from (up to) half the lower-risk participants to impute these additional visit data for the remaining participants if it seems bias will otherwise arise. We prefer not to impute visits out of the study area unless this is required because the data on visits outside the area by lower-risk participants are only approximate.

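### The unqualified rule that women who move are lost to follow-up contradicts the plan's own tracking, survey and analysis sections and, if applied literally, would end telephone ascertainment for a selected group

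*Protocol article*

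**What the plan says.** The paragraph under Fig. 1 in the protocol article sets follow-up to run "up until the expected baby is 1 year of age" and then adds: "Participants who move out of the study location are considered lost to follow up". Study location is not defined there. It could mean the facility catchment used for eligibility, or Siaya County, which the card-reader section calls the evaluation zone.

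Other sections bear on the same women:

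- **Collecting data on visits to facilities outside the study area.** High-risk women are tracked into neighbouring counties. For care outside Western Kenya, a single instance is missing data, "or the participant will be classed as lost to follow up if they have permanently transferred". For lower-risk women in the telephone sample, "we shall also ask whether the participant moved temporarily or permanently outside the study area".
- **Table 1.** Migration away from the study area is a key covariate, with telephone surveys 1, 3 and 4 among the sources for covariates.
- **Trial participants.** "Access to a mobile phone is a project requirement for the cash transfer payments and participant follow up".
- **Telephone surveys.** On the reach of survey three: "A telephone survey is administered to 50% of participants 6 months after the EDD". Its questions cover deaths of mothers and children, how each is faring, infant feeding and contraception. Survey four, at 12 months, goes to the women who completed survey three. Survey two goes to women without a facility delivery.
- **Final analysis.** "Final analyses will be by intention-to-treat, based on all enrolled mothers". An attendance with no record in the study area counts as not attended. Telephone reports of out-of-area visits may be used for imputation if bias seems likely.
- **Interim analysis.** Infant and maternal mortality are the two key safety measures.

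**The concern.** The plan gives field staff two incompatible instructions for a woman who moves. Under the Fig. 1 sentence she is lost at once, whatever the outcome. Under the out-of-area section she is still tracked if high-risk, or still called and asked about the move if she is in the telephone sample.

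Which instruction is followed matters because the main telephone outcomes do not depend on where the woman lives. Vital status, self-rated and infant health, breastfeeding and contraception can be obtained by a call to another county, whereas local clinic records cannot replace that call for a woman who has left. Because survey four goes only to those who completed survey three, a woman dropped at 6 months is also lost at 12.

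Moving is a post-randomisation event. It may follow illness or bereavement. It may also differ by arm, since payments are tied largely to visits within Siaya County. Ending ascertainment at the move therefore risks selective loss. It would also undermine the out-of-area bias check, because the women best placed to report such visits would not be called and the check would rest on those who stayed.

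**Working it through.** **1. The sections side by side.**

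| Question | Paragraph under Fig. 1 | Elsewhere |
|---|---|---|
| High-risk woman moves to a neighbouring county | Lost | Tracked; lost only on permanent transfer outside Western Kenya |
| Lower-risk woman in the telephone sample moves | Lost | Asked whether the move is temporary or permanent, so she must still be called |
| Migration | Ends follow-up | A covariate collected partly in surveys 3 and 4 |
| Out-of-area visits | No source once she is lost | Telephone reports support the bias check and possible imputation |

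The two columns cannot both be carried out.

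**2. Women affected.** The plan states no figure for movers, so there is none to reproduce. Inputs: 7,200 women (Sample size); 50% in surveys three and four (Telephone surveys); infant mortality 111 per 1000 (Study setting). Assumptions: a mover rate of 5–15% before the child's first birthday, the same in the sampled half, and one live-born infant per woman. The introduction to the telephone surveys speaks of all participants, but the entries for surveys three and four give 50%, and that figure is used here.

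- Sampled women: 7,200 × 0.50 = 3,600.
- Sampled women who move: 3,600 × 0.05 = 180 to 3,600 × 0.15 = 540.
- Infant deaths among their children: 180 × 0.111 ≈ 20 to 540 × 0.111 ≈ 60, out of 3,600 × 0.111 ≈ 400 in the sampled half.

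The 20–60 is an upper bound for average-risk movers, since it treats every death as coming after the move. Losses through survey two cannot be sized, because the number of movers without a facility delivery is not given.

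**3. Selection.** Suppose the true infant risk is 11.1%, a fraction d of women move, movers carry r times the stayers' risk, and all their deaths fall after the move. The risk seen in stayers is 0.111 / (1 − d + d·r).

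| d | r = 1.5 | r = 2 |
|---|---|---|
| 5% | 0.111/1.025 = 10.8% | 0.111/1.05 = 10.6% |
| 15% | 0.111/1.075 = 10.3% | 0.111/1.15 = 9.7% |

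If d and r are equal in both arms, both arms are understated alike. If one arm has d = 5% and the other 15%, with r = 2 and no true effect, the observed risks differ by about 10.6 − 9.7 = 0.9 percentage points. Both r values are assumptions.

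**4. Power is a minor issue.** The plan's design effect reproduces: 1 + 149 × 0.005 = 1.745, and 3,600/1.745 = 2,063 per arm; 1 + 149 × 0.025 = 4.725, and 3,600/4.725 = 762. If 15% of every cluster were lost, the cluster size would be 127.5. The effective sizes would then be 3,060/(1 + 126.5 × 0.005) = 1,874 and 3,060/(1 + 126.5 × 0.025) = 735. Power at the plan's stated differences, two-sided 5%, goes from 82.5% and 82.9% to 78.8% and 79.2% (low ICC), and from 83.6% and 81.2% to 82.3% and 79.8% (moderate ICC). This overstates the loss for the primary outcomes, where an unfound attendance is still scored. The stake is selective loss of telephone outcomes.

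**The case against.** The strongest reply is that the document nowhere says calls stop or collected data are dropped when a woman moves, and that several sections assume the contrary. That stands. A reader might infer from the Fig. 1 sentence that obtainable safety and secondary-outcome data are being discarded. The documents support only a contradiction, with that loss as the result if the sentence is applied literally.

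Four further limits also stand.

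- A reader might apply the mover rate to all 7,200 women and reach 40–120 infant deaths. That is about double what surveys three and four could capture, because they cover half the women.
- The secondary mortality outcomes end 48 hours after birth, before most postnatal moves. They could be affected mainly by a move in pregnancy that costs the survey two call. Later deaths matter for the mortality reports to the Data Management Committee, whose data source is not stated.
- Reachability is not assured. The eligibility criterion allows a phone belonging to a household member or another trusted person, and a woman who moves may leave that phone behind.
- A reader might see a breach of intention-to-treat. Being classed as lost to follow-up makes data missing; it does not remove a woman from the set of all enrolled mothers, and her unfound attendances are still counted.

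It can also be said that Fig. 1, the additional files and the analysis plan may define loss more fully. That does not remove a rule stated here without qualification, and an analysis plan cannot recover interviews that were never held.

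**Conclusion.** The concern holds as an internal contradiction with a practical consequence. The sentence under Fig. 1 cannot be reconciled with the out-of-area section, with the covariate sources in Table 1, or with the telephone-based bias check in the final analysis. If it is followed literally, telephone ascertainment ends after a post-randomisation event that may relate to outcome and arm.

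The size rests on an assumed mover rate of 5–15%: about 180–540 of some 3,600 sampled women, and at most about 20–60 infant deaths at the county rate. The true figure is smaller to the extent that deaths precede the move, movers cannot be reached, or staff already follow the out-of-area section. The wording should be corrected; the documents do not show that data have been lost.

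**What to change.** Reconcile the Fig. 1 paragraph with the out-of-area and final-analysis sections:

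1. Limit the moving rule to the ascertainment of facility visits, and only where the out-of-area section says so, including its permanent-transfer rule. Define study location.
2. State that women who move stay in whichever telephone surveys they are scheduled for, including vital status, unless they withdraw or cannot be reached after the planned call attempts. For telephone outcomes, lost to follow-up then means not reached or withdrawn.
3. Report the number of movers, and the number reached, by arm.

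The cost is a wording change, a call-list instruction and some extra call attempts. The calls are already part of the schedule and need no travel. Some movers will still be missed where the phone belongs to someone else. With recruitment closed on 31 July 2018 and the protocol version dated 26 December 2018, many 6- and 12-month calls would still have been due at that version.
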